### Exposure to UVB

To augment other information (outdoor activity, mobilization of fat stores or milk intake) as related to vitamin D status, exposure to sunshine, typical clothing habits, duration and frequency of exposure to sun, travel, and use of sunscreen are assessed using a questionnaire, which is found in the CHQ. To compliment this questionnaire, we measure skin pigmentation using a computerized narrow band reflectometer spectrophotometer (CM-700d/600d, Konica Minolta, Ramsey, NJ, USA). The spectrophotometer provides measures of melanin content of the skin or *Melanin Index* which has been shown to influence circulating 25(OH)D concentrations [77]. Measurements performed on the unexposed skin of the inner upper arm have higher correlation to the *Melanin Index* than measurements performed on the exposed forehead [78] according to standard guidelines [79]. At each visit, skin pigmentation established by measuring pigmentation three times at each site for constitutive pigmentation at the inner upper arm and facultative pigmentation at the forehead, mid-forearm and lower leg using the spectrophotometer. Individual typological angle (ITA^o^) is calculated with the L* and b* values using the equation from the Commission D’Éclairage [80] and are classified into 6 skin types based on Fitzpatrick descriptions [81,82].

### Parental perception of child eating behavior

Parents self-report on their child’s eating behaviour by completing the Child Eating Behaviour Questionnaire (CEB-Q) [83]. This validated questionnaire for children 4 to 13 requires parents to score 35 questions identifying different eating behaviours as “never”, “rarely”, “sometimes”, “often” or “always” [84-86]. This 2-pg survey identifies 7 eating styles: (1) food responsiveness; (2) enjoyment of food; (3) emotional overeating; (4) under eating; (5) desire to drink; (6) satiety responsiveness and slowness in eating; and (7) fussiness. The CEB-Q is completed at each research visit to help identify changes in child’s eating styles throughout the year and interventions. Unique to other studies, this questionnaire is used to individualization of the intervention sessions, by guiding the interventionist to discuss and prioritize negative eating behaviours. This questionnaire is part of our CHQ.

### Child intention and self-perception of nutrition and physical activity

A series of questions asked by a trained researcher to the child was created on the basis of the theory of planned behaviour [87]. Briefly, this theory postulates that human behaviour is guided by behavioral beliefs (e.g. consequences or attributes of the behavior), normative beliefs (e.g. expectations of others) and control beliefs (e.g. presence of factors that hinder or enhance behavior) [88]. These concepts are captured in the Child Intention Questionnaire (CIQ), a questionnaire that is research-administered every visit and asks children about their intentions and behaviours for engaging in physical activity, self-perception, attitude towards physical activity and nutrition and behavioural control [89,90]. Children self-identify themselves by identifying a picture that best describes them. The concept of self-perception is identified as it will influence decision making and ultimately the child’s actions [91]. Using a gender specific 5-point visual analogue scale, children identify how they feel about certain activities. Intensity of activity is determined using a gender specific Rated Perceived Exertion Scale [92]. With parental permission, this questionnaire is completed without the presence of the parents or family. This type of questionnaire is important to include in a study of this nature, as it identifies concepts that are important in weight interventions, especially when evaluating the family’s confidence in achieving a particular goal or changing a behavior. If interventions do not include such questions, it is likely goals will not be met and negative feelings towards the program may occur [91].

### Intervention

In line with the Transtheoretical Model [15] and the Theory of Planned Behavior [93], this study is based on similar principles of the “Obeldicks Light” framework [94]. Our intervention is based on physical activity, nutrition education and behavioral counselling. Interventions are family-centered and use motivational interviewing techniques, specifically engaging in reflective listening, sharing decision making with the child and families, and setting realistic goals with the child [95]. For example, the interventionist suggests goals to the child and as a group, all present discuss how the goals will be attained. A goal is never set unless the child agrees to the goal and can independently strategize how they can achieve the goal in a realistic manner. All members of the family are encouraged to participate in the interventions particularly those caregivers who have a direct impact on the child’s eating and activity (i.e. meal preparation, afterschool care etc.).

Intervention sessions are held at the end of each of the first 5 mo of the study, at the end of 8 mo, concluding with a debriefing session at 12 mo. Families participate in a total of 9 hours of counselling, based on 5 × 1.5 h visits at the end of months 1 through 5. The additional visit at the end of 8 months (1.5 h) is used to determine if new diet and activity intervention strategies are necessary over time as the child grows/matures and due to season. Counselling visits at the end of months 2, 5 and 8 overlap with regular study visits and are conducted after study data is collected to limit leading and bias (same day if need be to limit travel). Table 2 outlines the overall study design. All interventions have been designed by and will be carried out by a bilingual registered dietitian with experience in physical education.

**Table 2 T2:** Differences among standard (StnInt) and modified (ModInt) treatment groups

** Standard intervention**	** Modified intervention**	**Control group**
**Nutrition recommendations **^**a**^		
Food servings per day^b^[9]:	Food servings per day^b^[9]:	Food servings per day:
•Vegetables and Fruit: 5	•Vegetables and Fruit: 5	•Will be based on the Canada Food Guide for their age.
•Grain Products: 4	•Grain Products: 4	
•Milk and Alternatives: 2	•Milk and Alternatives: 4	
•Meat and Alternatives: 1	•Meat and Alternatives: 1	
**Physical activity recommendations **^**a**^		
**Cardiovascular Recommendations**		
Frequency: 7 days	Frequency: 7 days	Frequency: 7 days
Intensity: moderate to vigorous	Intensity: moderate to vigorous	Intensity: moderate to vigorous
Type: cardiovascular	Type: cardiovascular	Type: cardiovascular
Time: 60 minutes	Time: 60 minutes	Time: 60 minutes
**Weight Bearing Recommendation**		
Frequency: 3 days	Frequency: 3 days	Frequency: 3 days
Intensity: light	Intensity: light	Intensity: light
Type: strength	Type: strength	Type: strength
Time: 30 minutes	Time: 30 minutes	Time: 30 minutes
**Sedentary activity**		
< 2 hours screen time per day	< 2 hours screen time per day	< 2 hours screen time per day

^a^ Children are encouraged to meet these recommendations for nutrition and physical activity. These recommendations are based on Canada’s Food Guide and the Canadian Physical Activity Guide. Children in the StnInt are reminded to engage in strength training activities, but the discussions are not as in depth as ModInt group.

^b^ If a child turns 9 their recommended to consume 6 Vegetables and Fruit; 5-6 Grains; 3 Milk and alternatives; 1 Meat and alternative.

The overall focus of the intervention is to help families make healthier lifestyle choices in terms of nutrition and physical activity, and to reduce screen time and other (sedentary behaviours). Differences between StTx and ModTx intervention lie in the CFG for children aged 4–8 y for all food group servings (Table 3). The modified intervention group is instructed to consume 4 servings of milk and alternatives per day. Although both interventions will be counselled to participate in 60-minutes of activity per day, special emphasis placed on activities that are also weight-bearing for ModTx. Examples of weight-bearing activities include jumping rope, brisk walking, dancing, racket sports (i.e. tennis) and soccer. Notably, these are also aerobic activities.

**Table 3 T3:** **Intervention protocol for standard (StnInt) and modified (ModInt) treatment groups**^**a**^

**Visit 1**	**Visit 2**	**Visit 3**	** Visit 4**	** Visit 5**	** Visit 6**
**Education**					
1. Review CFG and PA guide^b^	1. Understanding Food labels^c^	1. Eating “out and about” (eating in other environments other than home)	1. Making a meal plan	1. Tricky situations	1. Staying on track
			2. Identifying hunger cues		
**Each session will also include discussions concerning:**					
•	Eating behaviours				
•	Reviewing the dairy intervention and strategizing how to stay on track				
•	Evaluating healthy food choices (Traffic light evaluation)				
•	Physical activity (frequency, type, time and intensity) discussion				
•	Sedentary activity (screen time) and provide alternative activities				
•	Relapse prevention through identification of a “tricky situation” (i.e. birthday party, vacation, holiday, sleepovers, rainy/ snowy days)				
•	Three SMART Goals				

CFGHE: Canada’s Food Guide to Healthy Eating, PA: Physical Activity.

^a^ Control group will receive the same visit format but at the end of 12-months of the study.

^b^ According to randomization, children are instructed to consume 2 or 4 servings of milk and milk alternatives per day.

^c^ Parents are encouraged to bring in food labels from home to ensure discussions are individualized.

All intervention sessions are recorded using a standardized tracking sheet for all components, ensuring all sessions follow the same structure with room for individualism and variety. Within each session, the dietitian identifies a key area that requires further discussion, which is either identified by evaluating the CEB-Q [83] or through parent concern or a concept that the interventionist has picked-up on during the session. This provides for individualization of sessions to meet family needs and to provide for self-directed change. All sessions are directed at the index child and are performed at the grade 1 reading and learning level.

### Components of the interventions

#### Education

The underlying principles of nutrition education are embedded in both StTx and ModTx groups. The goal of the education sessions is to improve self-efficacy through empowerment of healthy choices and behaviors. Table 2 details the education topics for each session. In brief, session 1 reviews the food and exercise guides. During session 2, families are taught how to read food labels and identify healthy food choices from labels using a tear-sheet from Health Canada [87]. Session 3 reviews eating out at restaurants or other environments. Session 4 asks children to create a meal plan using food models; during this session children are also taught about different types of hunger, a concept modeled from the Craving Change© series that focuses on three types of hunger (E.g. “tummy hunger”, “mouth and eye hunger” and “heart hunger”) [96]. Sessions 5 and 6 are open to reviewing concepts already discussed, and are necessary to discuss relapse prevention and reinforce positive lifestyle and behavioral changes. In line with TTM, sessions 5 and 6 are critical components of an intervention program as it ensures children and parents are able to remain in the action phase of change [15]. In addition, these sessions are used to increase self-efficacy of the child by discussing challenges that may arise and how to sustain positive thinking and motivation to stay on track.

#### Nutrition intervention and nutrition evaluation

According to the randomization, the dietitian counsels children to consume either 2 servings per day or 4 servings per day of milk and alternatives. Two servings per day is the recommendation for this age group (6–8 y). The child is given a certificate to remind parents of their specific milk and alternative requirements. Parents are also provided with the extended Health Canada list of milk and alternatives to ensure they understand this food group well. At this time, the dietitian works with the parents and child to strategize ways they can meet their recommendation. Ethically, and in line with Canada’s Food Guide, children who turn 9 will be instructed to consume 3 or 4 servings of milk and alternative as the recommendations suggest, but 3 per day accepted as meeting the servings.

At every intervention, parents and children complete a 24-h recall. Using the recall, the dietitian reinforces the appropriate quantity of milk and alternatives according to their group. If they are not meeting the recommendations, time is taken to discuss measures to get back on track and to identify barriers to change. Children are evaluated on their understanding of healthy snack choices using a modified traffic light diet evaluation, a form of evaluation often used with children [97]. The original traffic light diet uses a color-coded, calorie based exchange system [98]. We used the same concepts of coloring food choices and ask children to identify “go to foods” (green), “foods that are healthy but when eaten too much become unhealthy (yellow), and “foods that should be avoided on a routine basis, or “sometimes foods” (red). If necessary, the interventionist coaches the child by repeating the description of the food classification, but does not answer for the child. The interventionist records the answers and categorized by food group, or extra-foods (salty, sugary).

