To our knowledge, there is no study that has examined the effects of a family-centered lifestyle intervention that investigated the altered bone structure [51] or modulators of bone health in addition to those that can reduce adiposity [52]. This paper shares a comprehensive approach that will be used in a randomized controlled trial of a 1-y lifestyle intervention in overweight and obese prepubescent children. This study will involve two levels of intervention: one focused on meeting recommended age-specific targets for nutrition and physical activity (standard intervention [StTx]) and a second focused on increased milk and alternatives consumption and weight-bearing activities (modified intervention [ModTx]) as a means to enhance support for bone mass. It is hypothesized that children receiving the ModTx will have a lower BMI Z-score, lower waist circumference and improved weight-for-age Z-score and increased bone mass and strength at 12-months compared to children in the StTx and control groups. Secondary objectives are to examine the effects of the intervention on changes of children’s eating behaviour throughout the intervention compared to control.

This study, the McGill Youth Lifestyle Intervention for Food and Exercise (MY LIFE Study), embraces the family-centered approach in a non-institutional setting. The primary focus of the MY LIFE Study is to create realistic nutrition and PA goals, while providing families with the necessary education and behavioral tools necessary to help the child meet their immediate and long-term goals of attaining a healthy lifestyle.

The study methods are in accordance with the CONSORT guidelines for reporting randomized trials [53]. Ethical approvals were obtained from McGill University Faculty of Medicine Institutional Review Board and Montreal Public School Boards. The MY LIFE Study is registered online at http://www.Clinicaltrials.gov (Trial # NCT01290016).

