## Methods/design

### Participants

Eligible participants are healthy children 6–8 y, living in or near Montréal, Québec, who are overweight or obese according to the World Health Organization weight-for-height BMI cut-off criteria [54]. In addition to parental consent, participants provide written informed assent by reading and signing an assent form written at the grade 1 level. Participants must be either English or French. Only one eligible child per household is included in the study. Exclusion criteria includes: 1) known or suspected serious, chronic illness of childhood, such as cancer, Crohn’s disease, nephrotic syndrome, rheumatic conditions, and diabetes, etc., or those with disturbances in bone, vitamin D or mineral ion metabolism including rickets, osteomalacia, liver disease, renal disease, immobilization (complete or partial), current fractures, and disorders of the parathyroid gland; 2) use in the past 3 months, medications known to affect bone and/or mineral ion metabolism including all glucocorticoids, phosphate therapy or vitamin D analogues and any bisphosphonates; 3) severe anemia precluding blood sampling (previously diagnosed); 4) established diabetes mellitus (any type) and 5) hyperlipidemia ascribed to non-dietary causes.

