### Randomization and blinding

Children are randomized by a computer-generated list using stratified block randomization of three per block to maintain balance. Two stratification factors are implemented: gender and BMI (overweight and obese). In order to maintain blinding for non-intervention related measurements, children are randomized to control, StTx or ModTx groups by the registered dietitian who conducts the interventions. Participants are informed of their group at the end of their baseline visit. All other research staff are blinded.

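### From age 9 the protocol no longer enforces a milk difference between ModTx and StTx, and every child who enters aged 8 reaches that age by the 12-month endpoint

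*Protocol article*

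**What the plan says.** - **Arm targets.** The Intervention section states: "The modified intervention group is instructed to consume 4 servings of milk and alternatives per day". Table 2 gives StTx 2. All other food-group, activity and screen-time figures in Table 2 are the same in the two treatment columns. Footnote a and the physical activity section add that ModTx receives more emphasis on weight-bearing activity.
- **Age 9, Table 2 footnote b**, marked on both treatment columns: "If a child turns 9 their recommended to consume 6 Vegetables and Fruit; 5-6 Grains; 3 Milk and alternatives; 1 Meat and alternative". It makes no distinction by arm.
- **Age 9, nutrition intervention section.** From the ninth birthday a child is "instructed to consume 3 or 4 servings of milk and alternative as the recommendations suggest, but 3 per day accepted as meeting the servings". Ethics and Canada's Food Guide are given as the reason. Neither number is assigned to an arm.
- **Table 3 footnote b**, attached to the first session: "According to randomization, children are instructed to consume 2 or 4 servings of milk and milk alternatives per day". It does not mention age.
- **Population and timing.** "Eligible participants are healthy children 6–8 y", with the primary outcome measured from baseline to 12 months.
- **Hypothesis (Background).** ModTx is expected to show a lower BMI Z-score and "increased bone mass and strength at 12-months compared to children in the StTx and control groups".

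**The concern.** Extra milk is one of the two features that separate ModTx from StTx, and the only one expressed as a number. The age-9 rule lets that number become the same in both arms, and a ModTx child on 3 servings counts as having met the target. The rule is not a rare exception, because the eligibility range and the length of follow-up bring every 8-year-old entrant under it.

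Any effect of milk on BMI Z-score or bone is then partly removed from the ModTx–StTx comparison by the plan itself, and a true difference is pulled towards zero. Adjusting for the milk intake recorded in the food diaries would not repair this, since achieved intake is not randomised.

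The stated ethical reason explains raising StTx from 2 to 3. It does not explain relaxing ModTx: the same sentence, and the Control section, put 4 servings within the recommendation from age 9.

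**Working it through.** **1. Who is affected.** A child aged 8.00 to 8.99 at entry is 9.00 to 9.99 at month 12, so all 8-year-old entrants have turned 9 by the endpoint. The protocol gives no entry-age distribution. Assumption: ages uniform from 6.0 to 9.0, so one third enter aged 8 (range shown: 20% to 50%). Per arm this is 39 × 1/3 = 13 children (39 × 0.2 = 8 to 39 × 0.5 = 20).

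**2. Milk contrast after the ninth birthday.**

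| Reading | StTx | ModTx | Contrast |
|---|---|---|---|
| Under 9 | 2 | 4 | 2 |
| Table 2 footnote b | 3 | 3 | 0 |
| Text, read as 3 for StTx and 4 for ModTx | 3 | 4 (3 accepted) | at most 1 |

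**3. Average prescribed contrast over the year.** An 8-year-old entrant spends on average 0.5 y at age 9, so the share of all child-time at age 9 is t = 1/3 × 0.5 = 0.167 (0.10 to 0.25). Contrast = 2(1 − t) + c·t, where c is the contrast from age 9.
- c = 0: 2 × 0.833 = 1.67 (1.80 to 1.50).
- c = 1: 1.667 + 0.167 = 1.83 (1.90 to 1.75).

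**4. If targets change only at counselling sessions** (ends of months 1–5 and 8). Birthdays in months 1 to 5 leave 11, 10, 9, 8 and 7 months on the new target, birthdays in months 6 to 8 leave 4 months each, and later ones leave none. The mean is (11 + 10 + 9 + 8 + 7 + 12)/12 = 4.75 months, or 0.40 y. The share switched is 1/3 × 8/12 = 22%, about 9 of 39 per arm. With c = 0, t = 1/3 × 0.396 = 0.132 and the contrast is 1.74.

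**5. The plan's own sample size.** With 0.2, SD 0.3, two-sided 5% and 80% power, n per arm = 2 × [0.3 × (1.960 + 0.842)/0.2]² = 35.3. Adding 10% gives 38.9, so 39 per arm, and 3 × 35.3 × 1.1 = 116.6, which agrees with the stated 116. This figure is not in dispute.

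**6. Illustrative power, ModTx versus StTx.** Two-sample t test, 35 per arm (39 × 0.9), no multiplicity adjustment. The difference is 0.2 at full contrast, and its milk-driven share m is assumed proportional to prescribed servings. Multiplier = 1 − m × (1 − contrast/2). One third aged 8 at entry, target changed on the birthday:

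| c | m | Multiplier | Power (20% to 50% aged 8) |
|---|---|---|---|
| no age-9 rule | – | 1 | 78.5% |
| 1 | 0.5 | 0.958 | 75% (76% to 73%) |
| 1 | 1 | 0.917 | 71% (74% to 67%) |
| 0 | 0.5 | 0.917 | 71% (74% to 67%) |
| 0 | 1 | 0.833 | 63% (70% to 54%) |

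Switching only at sessions, the c = 0, m = 1 case becomes 1.74/2 = 0.868, power 66.5%.

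**The case against.** - **The text may keep a contrast.** The paragraph opens with 2 or 4 servings by randomisation, so 3 or 4 may be meant in parallel: StTx 3, ModTx 4. This is a fair reading. But the sentence does not assign the numbers, it accepts 3 without limiting that to StTx, and footnote b gives 3 alone. An enforced difference is therefore still absent.
- **The Intervention section could be read as giving 4 servings at any age.** It does not. The preceding sentence ties the arm differences to the guide for ages 4–8, and footnote b supplies the age exception. Only Table 3 footnote b is silent on age, and it annotates the first visit.
- **A reader might infer that power falls to 63%.** The documents do not support that as a finding. It needs a BMI Z-score effect that is wholly milk-driven and proportional to prescribed servings, a contrast of 0, an assumed age mix, and a switch on the birthday. The Background itself calls the role of milk in body weight unclear, and the sample size section does not say that −0.2 is the ModTx–StTx difference.
- **A reader might also infer that age should be stratified or 8-year-olds excluded.** Randomisation does use only gender and BMI class, but the rule dilutes the contrast whether or not age is balanced. Excluding 8-year-olds changes the target population and, on the same assumption, loses about a third of it.
- **The change is declared and has an ethical reason.** True, and that reason supports StTx moving to 3. It does not require ModTx to leave 4.

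**Conclusion.** The point stands in limited form. From age 9 the protocol removes the enforced milk difference between ModTx and StTx, and its two statements of the age-9 target do not match. All children who enter aged 8 come under the rule by month 12; their number is unknown (about one third if entry ages are uniform, about 22% if targets change only at counselling sessions). For them the contrast drops from 2 servings to 0, or at most 1, for part of the year.

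The effect is a dilution of the milk component of one comparison. The ModTx emphasis on weight-bearing activity persists, and ModTx versus control is little affected because control families receive their counselling sessions only after the study year. The power range of 63% to 75% against 78.5% shows what might be lost under stated assumptions; it is not an estimate. No size can be given for bone, where the protocol states no effect or SD. The loss is small to moderate, and part of it is avoidable within the protocol's own recommendation.

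**What to change.** State in the nutrition intervention section that from age 9 the target is 3 servings in StTx and 4 in ModTx, and that 3 is accepted as meeting the target in StTx only. Give the same arm-specific figures in Table 2 footnote b. The cost is wording alone, and both targets stay within the 3 to 4 servings the protocol cites for this age. It does not restore the full contrast: 1 serving remains from age 9 instead of 2, because StTx has to rise.

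Optionally, add a supportive analysis of ModTx versus StTx in children under 8 at entry, who keep the 2-serving difference all year. Age at entry is a baseline variable, so the comparison remains randomised. With about 26 of 39 per arm on the uniform-age assumption, its precision is low and it should not be used as a test. No change to eligibility or to the stratification factors is needed.
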